### Eligibility and baseline assessment

For each included participant, the following baseline characteristics will be collected:Demographic information: gender, age, weight (kg), height (cm), education, nationality, registered residence (rural or urban), permanent address;Clinical information: Chief complaint, symptoms, indications, signs, baseline mRS;Medical history: History of intracranial aneurysms, history of head surgery, family history of SAH and intracranial aneurysms, comorbidities such as hypertension, diabetes mellitus, and cardiovascular disease;Lifestyle habits: Smoking, drinking, sleep pattern, exercise, occupation;Life quality evaluation: EuroQol 5-Dimensional, 5-Level (EQ-5D-5L) scores, sleep and psychosocial indexes (Shift Work Assessment, Pittsburgh Sleep Quality Index (PSQI), Patient Health Questionnaire-9 (PHQ-9), Hospital Anxiety and Depression Scale (HADS), Short-Form 36 Health Survey (SF-36);Information from the head CTA and report: Radiology report of head CTA, details on the number, location, size, and morphology of aneurysms, time taken for interpretation, PHASES score [26], and ELAPSS score [27] for unruptured and untreated aneurysms;Others: AI interpretation results, time of Workstation manipulation.

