#### Secondary outcomes (Table S1)

Differences of other diagnostic performance metrics for intracranial aneurysms between True-AI and Sham-AI group, including accuracy, lesion-level sensitivity, positive predictive value (PPV), and negative predictive value (NPV).Differences of the diagnostic performances for other intracranial lesions between True-AI and Sham-AI group, including patient-level sensitivity, specificity, accuracy, PPV, and NPV for intracranial arterial stenosis (≥ 50%), occlusion, and intracranial tumors.Differences of the detection rates of intracranial lesions according to radiology reports between True-AI and Sham-AI group, including intracranial aneurysms, intracranial arterial stenosis (≥ 50%), occlusion, and intracranial tumors.Differences of the workload of head CTA interpretation between True-AI and Sham-AI group, including the time (seconds) of interpreting head CTA images and the number of consensus meetings (times).Differences in the proportion of participants with resource use between True-AI and Sham-AI group, including the number of care encounters (in person) during follow-up, the number of care encounters (in person) for aneurysms during follow-up, and the total number of cerebral artery tests (including DSA, CTA, MRA, and high-resolution vessel wall MR imaging) at the 3-month and 12-month follow-ups.Differences in the proportion of participants with treatment-related clinical events between True-AI and Sham-AI group including clinical follow-up, hospitalization (number of subsequent hospitalizations, number of hospitalization for intracranial aneurysms, in-hospital mortality rate, morbidity with modified RS ≥ 3 due to intracranial hemorrhage or treatment, length of hospital stay), patients undergoing DSA (detection rate of intracranial aneurysms among DSAs, detection rate of no abnormality among DSAs), patients with different methods for aneurysm treatment (conservative/coil/clip/others), patients with aneurysm treatment-related complications (intraoperative rupture, death, stroke, etc.), patients with recurrence or residual intracranial aneurysm after surgery at the 3-month and 12-month follow-up.Differences of life quality evaluation between True-AI and Sham-AI group including EQ-5D-5L scores, sleep and psychosocial indexes (shift work assessment, PSQI, PHQ-9, HADS, SF-36, mRS) at both the 3-month and 12-month follow-up assessments.Differences in the proportion of participants with outcomes of aneurysm-related events between True-AI and Sham-AI group including all-cause mortality, mortality of aneurysm rupture, aneurysm growth, aneurysm rupture, SAH, and stroke (hemorrhagic stroke, ischemic stroke) at the 3-month and 12-month follow-ups.Differences in the incremental cost-effectiveness ratio (ICER) between True-AI and Sham-AI group at 3-month and 12-month follow-up. We will calculate quality-adjusted life years (QALYs) by using the EQ-5D-5L life quality questionnaire at the 3-month and 12-month follow-up for the True-AI and Sham-AI arms. Healthcare costs per patient will be calculated as the sum of inpatient, outpatient, testing, and pharmaceutical costs during the follow-up period for the two arms. We will divide the difference in healthcare costs by the difference in QALYs to calculate the ICER of the True-AI arm compared to the Sham-AI arm. To determine whether the True-AI arm is cost-effective, we will use cost-effectiveness thresholds with an ICER < $38,070 per QALY gained will be considered cost-effective (Highly cost-effective was defined as an ICER less than 1 time the per capita gross domestic product (GDP) in China; cost-effective, an ICER of 1 to 3 times the per capita GDP; and not cost-effective, an ICER greater than 3 times the per capita GDP [32]. The per capita GDP in China in 2023 was US $ 12,690). We will conduct deterministic sensitivity analysis on all QALYs and cost parameters, typically by one-way or two-way sensitivity analyses. One-way sensitivity analysis involves systematically varying individual parameters through plausible values while holding all other values constant and assessing the impact of these individual variations, while two-way sensitivity analysis involves varying two parameters simultaneously. Our sensitivity analysis will address the uncertainty in the estimation of QALYs and cost parameters and assess its impact on cost-effectiveness results.

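### The cost-effectiveness outcome leaves the cost of the AI out of the ICER, plans only deterministic variation for uncertainty, and gives graded labels with no condition on the sign of the differences

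*Protocol article*

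**What the plan says.** All the main elements are in the protocol article under Secondary outcomes (Table S1).

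- Costs: "Healthcare costs per patient will be calculated as the sum of inpatient, outpatient, testing, and pharmaceutical costs during the follow-up period".
- Ratio: "We will divide the difference in healthcare costs by the difference in QALYs to calculate the ICER".
- Decision threshold: "we will use cost-effectiveness thresholds with an ICER < $38,070 per QALY gained will be considered cost-effective".
- Top grade: "Highly cost-effective was defined as an ICER less than 1 time the per capita gross domestic product (GDP) in China". The next grade runs from 1 to 3 times GDP, and anything above 3 times is not cost-effective. GDP per capita is given as $12,690.
- QALYs are obtained "by using the EQ-5D-5L life quality questionnaire at the 3-month and 12-month follow-up".
- Uncertainty: "We will conduct deterministic sensitivity analysis on all QALYs and cost parameters", described as one-way or two-way.

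Elsewhere, Eligibility and baseline assessment lists "Life quality evaluation: EuroQol 5-Dimensional, 5-Level (EQ-5D-5L) scores" among the baseline data. Reading time is a workload outcome, and Data collection says that the workstation logs it for each case. Under Interventions, both arms go through the same workstation and interface.

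**The concern.** The cost list covers what happens to the patient after the scan. It does not cover what is done to the scan, which is the only thing that differs between the strategies. The sham design adds to the problem: the same workstation serves both arms, so even a full tally of costs incurred in the trial could cancel the AI cost out of the difference. It enters the ICER only if it is charged to True-AI explicitly. The same holds in part for reading time, because Sham-AI also presents suggestions that the radiologist must reassess.

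Two further features make the verdict fragile. Varying parameters one or two at a time shows how the ICER responds to chosen values. It does not show how far patient-level differences could move by chance. And a ratio compared with a cut-off is unambiguous only when the QALY difference is positive; the graded labels do not say so.

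At stake is a published statement that AI-assisted reading is, or is not, cost-effective, from a trial whose stated purpose is to inform clinical deployment.

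**Working it through.** **Threshold.** 3 × 12,690 = 38,070. The plan's figure reproduces exactly.

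**Who is affected.** Inputs from Sample size calculation: prevalence 12%, sensitivity 0.65 to 0.75, specificity 0.90 to 0.88.
- Extra true detections: 0.12 × 0.10 = 1.2% of patients.
- Extra false positives: 0.88 × 0.02 = 1.76% of patients.

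If a detection is worth g QALY and a false positive costs f QALY, the mean difference is 0.012g − 0.0176f. It is negative once f exceeds 0.012/0.0176 = 0.68 of g. The documents give neither g nor f, so the sign is unknown. The Discussion itself raises unnecessary repair, anxiety and depression as possible harms.

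**Size of the omitted cost.** Assume f = 0, no difference in the listed costs, and g from 0.005 to 0.10 (not in the documents).
- Mean QALY difference: 0.012 × 0.005 = 0.00006, up to 0.012 × 0.10 = 0.0012.
- AI cost per scan that uses up $38,070 per QALY: 0.00006 × 38,070 = $2.3, up to 0.0012 × 38,070 = $46.
- The same at $12,690: $0.8 to $15.
- The ICER shifts by AI cost divided by the QALY difference. At a difference of 0.001, $10 per scan adds $10,000 per QALY.

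**Sign condition.** Compare the literal label with net monetary benefit, NMB = 38,070 × ΔQALY − Δcost. The differences are illustrative.

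| Δcost | ΔQALY | ICER | Literal label | NMB |
|---|---|---|---|---|
| +$50 | −0.002 | −25,000 | highly cost-effective | −$126 |
| −$50 | −0.002 | +25,000 | cost-effective | −$26 |
| −$100 | −0.002 | +50,000 | not cost-effective | +$24 |

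In all three rows the literal label and the net benefit disagree.

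**Sampling error.** 6450 × 0.95 / 2 gives about 3063 per arm. The 5% is the protocol's allowance for withdrawn consent, not a rate of completed EQ-5D. Assume a QALY SD of 0.05 to 0.20 and a cost SD of $1,000 to $6,000 (not in the documents).
- SE = SD × √(2/3063), giving 0.0013 to 0.0051 QALY and $26 to $153.
- With no true difference in cost or QALYs, a simulation (normal, independent differences, 400,000 draws) gives a literal ICER below $38,070 with probability 0.60 to 0.96. If a positive QALY difference is also required, the probability is 0.30 to 0.48.

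Deterministic variation does not reveal either probability.

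**Baseline EQ-5D.** Assume a utility SD of 0.1 to 0.2 and a correlation of 0.5 to 0.7 between baseline utility and later QALYs. A one-SE chance imbalance moves the one-year QALY difference by 0.0013 to 0.0036, or $49 to $136 at $38,070. Baseline adjustment removes most of that noise.

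**The case against.** The best defence is that a journal article condenses the plan, and that unit costs, dominance rules and resampling methods commonly sit in a health-economic plan that is not shown. That is fair for what the article merely leaves out. It does not cover the cost sum, which the article states as a closed list, or the uncertainty method, which it names and says will address the uncertainty.

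Several stronger readings are tempting, and the documents do not support them.
- A reader might infer that any ICER below $38,070 counts as cost-effective even when QALYs are lost. The threshold is worded per QALY gained, which can be read as limiting it to gains. On that reading the first two rows of the table are no longer mislabelled, but the loss quadrants have no rule.
- A reader might infer that uncertainty is ignored. It is not: deterministic analyses are planned, and bootstrap methods are not excluded. The accurate criticism is that the one method stated does not quantify sampling error.
- A reader might infer that QALYs will use follow-up EQ-5D alone and so be biased. The article names the follow-up assessments but does not exclude baseline, and randomisation removes systematic imbalance. What remains is precision, and a starting value for the first three months.
- A reader might take one assumed gain per detection, count detections only, and quote a single expected QALY difference. That passes over the false positives implied by the protocol's own specificities.

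**Conclusion.** The point holds in this form. As written, the cost sum leaves out the intervention's own cost, which biases the ICER towards True-AI. This rests on the text alone and is the firmest part. The stated uncertainty method cannot quantify sampling error. The graded labels either mislabel results in which QALYs are lost or, if the threshold wording is read as limited to gains, leave them without a rule.

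The size is conditional. The $2.3 to $46 per scan spans a 20-fold range because it rests on an assumed QALY value per detection and on false positives costing nothing. The simulated probabilities rest on assumed SDs. The documents give no AI price, so whether the omission would reverse the verdict cannot be said; the range shows that a modest price could be enough. The coprimary endpoints and the sample size are unaffected.

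**What to change.** - **Cost.** Add an AI cost per scan (licence, hardware, and reading time from the workstation log) to the True-AI arm, over a stated range. State that it is charged to True-AI although both arms use the workstation.
- **Decision rule.** Base the verdict on incremental net monetary benefit at $12,690 and $38,070 per QALY, with a patient-level bootstrap interval. Report the cost-effectiveness quadrant alongside any ICER. Keep the deterministic analyses for unit costs such as the AI price.
- **QALYs.** State that QALYs are computed as the area under the curve from the baseline EQ-5D-5L and adjusted for it. This is a gain in precision, not a correction of bias.

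Most of this is wording and uses data already planned. The exception is the AI unit cost, which the documents do not say is collected and which must be obtained. True-AI may then look less favourable.

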
### Ethical safety outcomes

Rates of intracranial aneurysms, intracranial arterial stenosis (≥ 50%), occlusion, and intracranial tumors from the final radiology reports will be calculated during the trial and compared with those for the previous 3 months. A reduction in positivity rates of no more than 5% during the trial period will be considered to meet the safety outcome; otherwise, the study will halt to find the reason at the site.

We will further evaluate the false-positive findings that require unnecessary follow-up tests or treatment and extra radiologists’ ruling out time, as well as the false-negative findings that may cause catastrophic consequences.

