### Participating center qualification

The 25 medical centers are located in 7 different geographical regions of China (North China, Northeast China, East China, Central China, South China, Southwest China, Northwest China). Each center is a tertiary care hospital and has experience in the diagnosis of intracranial aneurysms, with an average of 250 patients undergoing head CTA examination each month. Thus, the cohort can adequately represent the population at the regional and national levels. These centers are needed to shut down other AI-based intracranial aneurysm detection models until patient enrollment is completed.

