### Participants and recruitment

Participants who fulfil the following criteria will be eligible:

Inclusion criteria:Adult inpatients and outpatients who are scheduled for head CTA scanning.

Exclusion criteria:Age under 18 years;Patients with contraindications to CTA;Modified Rankin Scale (mRS) score > 3;Refusal to sign informed consent;Participation in other clinical studies of intracranial aneurysms;Patients with failed head CTA scanning or incomplete image data or poor image quality.

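### The site-halting safety rule leaves its 5% limit undefined: as an absolute limit on the arm-pooled rate it barely registers lost sensitivity in the Sham-AI arm, and as a relative limit it lies well inside site-level sampling noise

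*Protocol article*

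**What the plan says.** Under Ethical safety outcomes, the article monitors four reported rates: "Rates of intracranial aneurysms, intracranial arterial stenosis (≥ 50%), occlusion, and intracranial tumors from the final radiology reports". They are "compared with those for the previous 3 months". The limit is "A reduction in positivity rates of no more than 5% during the trial period will be considered to meet the safety outcome", and the consequence of exceeding it is "otherwise, the study will halt to find the reason at the site". Threshold, comparator and consequence are therefore all fixed here. The scale of the 5%, the handling of the two arms and the number of lesion types needed to trigger are not.

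Two other sections bear on the comparator. Participating center qualification says "These centers are needed to shut down other AI-based intracranial aneurysm detection models until patient enrollment is completed", and describes the centers as tertiary hospitals "with an average of 250 patients undergoing head CTA examination each month". Participants and recruitment excludes patients with "Modified Rankin Scale (mRS) score > 3".

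**The concern.** The specific risk in a placebo-AI design is that readers in the Sham-AI arm miss lesions they would otherwise have reported. A rule meant to detect this should respond when it happens and stay quiet when it does not.

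Three features work against that:

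- If the arms are pooled, a higher reported rate under True-AI offsets a lower one under Sham-AI.
- Reported positivity counts false positives, so extra false positives can hide missed lesions.
- A raw difference at one site is noisy, and the text gives no tolerance for noise.

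This is the only halting rule in the article. If it is too blunt, it gives false reassurance. If it is too sharp, sites stop for no reason and the halts lose their meaning.

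**Working it through.** **Inputs from the documents.** Sample size calculation: prevalence 0.12; sensitivity 0.65 (Sham-AI) and 0.75 (True-AI); specificity 0.90 and 0.88; N = 6450. Study design: 25 sites, 1:1 within site. Participating center qualification: 250 CTAs a month on average. So there are 3 × 250 = 750 historical scans and 6450/25 = 258 trial scans per site (129 per arm).

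**Check of the inputs.** They reproduce the plan's sample size for sensitivity: 329 per arm, 329/0.95 → 347, total 694, and 694/0.12 → 5784. The safety rule has no stated operating characteristic to reproduce.

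**Assumptions.** Before the trial, readers perform at the Sham-AI planning values; case mix is equal; only enrolled patients count; there is one look.

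**Aneurysm positivity** = prev × sens + (1 − prev) × (1 − spec).

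- Baseline: 0.12 × 0.65 + 0.88 × 0.10 = 0.166
- True-AI: 0.12 × 0.75 + 0.88 × 0.12 = 0.1956
- Pooled as planned: (0.166 + 0.1956)/2 = 0.1808
- True-AI excess: 2.96 points, of which 1.2 are true positives (0.12 × 0.10) and 1.76 are false positives (0.88 × 0.02)

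**Absolute reading, arms pooled.** P(trigger) = Φ((drop − 0.05)/SE), with SE = √(0.166 × 0.834/750 + p(1 − p)/258) and p the pooled trial rate.

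| Scenario | p | Expected drop (points) | SE | P(trigger) |
|---|---|---|---|---|
| No change in either arm | 0.166 | 0 | 0.0269 | 3% |
| Planned True-AI gain | 0.1808 | −1.5 | 0.0275 | 1% |
| Sham-AI sensitivity halved (arm rate 0.127), True-AI gain | 0.1613 | 0.5 | 0.0266 | 4% |
| Sham-AI sensitivity zero (arm rate 0.088), True-AI gain | 0.1418 | 2.4 | 0.0256 | 16% |
| Sham-AI sensitivity zero, no True-AI gain | 0.127 | 3.9 | 0.0248 | 33% |

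**Absolute reading, Sham-AI arm alone (129 scans).** The expected drop reaches 5 points when sensitivity has fallen by 0.05/0.12 = 0.417, that is, to about 0.23. Trigger probabilities are about 84% at zero sensitivity (drop 7.8 points), 37% when it is halved and 8% with no change.

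A lesion type whose historical rate is below 5% cannot fall by more than 5 points, so on the absolute reading it can never trigger.

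**Relative reading, arms pooled.** The aneurysm limit is 0.05 × 0.166 = 0.0083, or 0.83 points. P(trigger) = Φ((0.95 × 0.166 − p)/SE), where the historical variance is multiplied by 0.95².

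- No change: Φ(−0.0083/0.0265) = 38%
- Planned gain: Φ(−0.0231/0.0272) = 20%

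If any one of the four rates can halt a site, simulation gives 87–90% with no change and 83–87% under the planned gain. This assumes independence and reported rates of 10–25% for stenosis, 3–8% for occlusion and 2–5% for tumor, none of which the documents give. If one composite rate is judged instead, 26–33% of sites halt with no change.

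**The case against.** **Is the absolute limit out of reach?** A reader might infer that it can never be reached. The figures do not support that. With zero Sham-AI sensitivity the expected pooled drop stays below 5 points, but the rule acts site by site: 25 × 0.157 ≈ 4 sites would be expected to cross, and at least one almost surely (1 − 0.843²⁵ ≈ 98.6%). The text also does not say that the arms are pooled, and a check on the Sham-AI arm would trigger at about 84% of sites. This stands. It does not rescue the pooled rule for a smaller but serious loss: with sensitivity halved, about 25 × 0.045 ≈ 1.1 sites would halt, against 25 × 0.031 ≈ 0.8 with no change.

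**Would most sites halt by chance on the relative reading?** A reader might infer this too. From documented figures alone the answer is 20–38%. A majority requires any-of-four triggering with assumed lesion rates, or repeated looks.

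**Is the comparator bias in the other direction?** If the historical period includes patients with mRS above 3 or AI-aided reads, its rate may be higher and a trigger more likely. With an illustrative historical rate of 20%, zero Sham-AI sensitivity would trigger at about 62% of sites. But the same shift raises the false-trigger rate under the planned gain from about 1% to about 14% (Φ((0.0192 − 0.05)/0.0281)), so it does not make the rule discriminate better. The article does not say whether the comparator is restricted, and prior AI use is only a possibility.

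**Is the stress scenario realistic?** Under Procedures, junior radiologists read without AI first and a senior reviews every report. Description of the investigational product reports noninferior reading with Sham-AI. Total loss of sensitivity is thus a test of the rule and not a prediction. A safety rule still has to be judged by what it would detect.

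**Is the detail in the Supplementary Appendix?** Data collection refers there for the safety evaluation. The look schedule and minimum scan counts may well be there and are not counted as omissions. The article nevertheless states a threshold with a consequence that cannot be applied as worded.

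**Conclusion.** The concern holds in a bounded form. The rule fixes a limit and a consequence but not the scale, the arm handling or the lesion criterion, and it ignores sampling error.

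As an absolute limit on the pooled aneurysm rate, it hardly separates a halving of Sham-AI sensitivity (4% of sites) from no change (3%), and it finds total loss at only 16–33% of sites. As a relative limit, it is 0.83 points against a standard error of about 2.7 points, with 20–38% chance halts on aneurysms alone at one look. The 83–90% figure for any of four lesions is conditional on assumed rates and independence.

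The results rest on average site size, equal case mix and pre-trial performance at the Sham-AI planning values. If all CTAs at a site were counted (about 3000 a year), the relative chance-halt rate with no change would be 28% for aneurysms alone and 78–83% for any of four. The primary estimates and tests do not depend on this rule. What is at stake is the protection it is meant to give and the avoidance of needless halts.

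**What to change.** 1. State whether the limit is absolute or relative, and whether each lesion type or a composite is judged.
2. Have an independent statistician compute the rates by arm and judge the Sham-AI arm separately, so that True-AI gains and false positives do not mask missed lesions. Keep investigators and radiologists blinded.
3. Replace the raw difference with a confidence-bound criterion, together with a minimum number of scans before a site is judged, or pool across sites.
4. Report the resulting false-halt and detection probabilities for a few stated losses of Sham-AI sensitivity. The size of the limit is for the sponsor to set.
5. Note as a limitation that the historical comparator may include patients with mRS above 3 and AI-aided reads. Restrict it only where the data already exist.

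**Cost.** Protocol wording and a small unblinded by-arm report. The statistician under Randomization is described only as generating the sequence, so this is an added duty that needs a firewall. Establishing mRS retrospectively for up to 25 × 750 = 18,750 historical scans would not be cheap, hence the limit in step 5. No extra patients are needed.
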